#### Strategies to improve adherence to interventions {11c}

Participants in the intervention group will log in to the WeChat MiniApp to complete the intervention sessions according to the schedule. “CBT ASCVD” will track the completion of each session. To improve adherence, the participants will receive positive and constructive feedback through the “clock-in” feature in the “CBT ASCVD” app. Participants will be able to “clock in” from the dashboard to routinely track if they exercise, take medications, and eat healthy.

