### Primary outcome measure

*LDL-C level*. The primary endpoint will be the mean change in LDL-C level [time Frame: from randomization (day 0) to V5 (week 24) for a total of 6 months of treatment]. Per guideline, the LDL-C level has been validated as a primary measurement for the clinical efficacy of the treatments [3].

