#### Methods in analysis to handle protocol non-adherence and any statistical methods to handle missing data {20c}

All patients who have received CBT for at least 4 weeks will be included in the full analysis set (FAS). Depending on the time investigated, the per-protocol (PP) analysis set will be made up of patients who complete the 6-month follow-up examinations. The FAS will be used as the basis for the primary analysis. If there is a discrepancy of greater than 10% between the FAS and PP samples, the analysis will be repeated for the PP analysis set. The safety population will include patients in the FAS. Unless otherwise noted, all analysis will be done in both the FAS and PP analysis sets.

There will be no replacement or imputation of missing values. All analysis will be based solely on observed cases. Patients who are loss to follow-up will be considered to have dropped out of therapy. Only the PP patients will be used in a sensitivity analysis to test the impact of this assumption.

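### The only sensitivity analysis for missing data is restricted to 6-month completers, so it cannot test what the week-24 primary analysis assumes about lost patients

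*Protocol article*

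**What the plan says.** All references are to the protocol article.

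- **Endpoint** (Primary outcome measure): "The primary endpoint will be the mean change in LDL-C level [time Frame: from randomization (day 0) to V5 (week 24"), described as six months of treatment in total.
- **Primary analysis set** (section {20c}): "The FAS will be used as the basis for the primary analysis". The FAS requires at least four weeks of CBT.
- **Missing data** (section {20c}): "There will be no replacement or imputation of missing values. All analysis will be based solely on observed cases". Patients lost to follow-up are classed as having dropped out of therapy.
- **PP set** (section {20c}): "the per-protocol (PP) analysis set will be made up of patients who complete the 6-month follow-up examinations".
- **Sensitivity analysis** (section {20c}): "Only the PP patients will be used in a sensitivity analysis to test the impact of this assumption".
- **When PP is run** (section {20c}): the analysis is repeated in PP "If there is a discrepancy of greater than 10% between the FAS and PP samples". A later sentence reads: "Unless otherwise noted, all analysis will be done in both the FAS and PP analysis sets".
- **Other analyses** (section {20b}): none.
- **Planned loss** (Sample size {14}): at most 20% in each group, with 150 patients per group.
- **Visits** (Outcomes {12} and section {18a}): baseline and months 1, 3 and 6.

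**The concern.** A sensitivity analysis for missing data should change the assumption made about the patients whose outcome is missing, and show whether the conclusion survives. This one removes those patients, and the primary analysis has already left them out by using observed cases only.

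The trial is open-label and compares a self-directed app with education given at follow-up visits, so it is plausible that patients who disengage are also those who leave. If so, the patients who remain may show a larger effect than all randomised patients would. Agreement between the FAS and PP results would then look like evidence of robustness without being any.

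The protocol does not leave this open for an analysis plan to settle. It fixes the no-imputation rule, names the sensitivity analysis and excludes additional analyses.

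**Working it through.** **1. Who contributes to each analysis of the primary endpoint**

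| Patient | FAS, observed cases | PP sensitivity analysis |
|---|---|---|
| At least 4 weeks of CBT, attends month 6, LDL-C measured | in | in |
| Stops CBT before week 4, attends month 6, LDL-C measured | out | in |
| At least 4 weeks of CBT, values at month 1 or 3, then lost | out (no week-24 change) | out |
| Lost before month 1 | out | out |

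The second row is possible because section {11b} keeps patients who stop treatment eligible for assessments. It shows that the two sets can differ. The last two rows are the lost patients, and they are absent from both columns.

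The assumption being tested could be the observed-case rule, or the classing of lost patients as having dropped out of therapy. PP omits the lost patients, so it tests neither.

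**2. The plan's own sample-size figure**

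Inputs from Sample size {14}: 122 evaluable per group, 20% maximum loss, 80% power, one-sided 0.05.

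- Dividing by the retained fraction: 122 / (1 − 0.20) = 152.5, so 153 per group.
- Multiplying up: 122 × 1.20 = 146.4, so 147 per group.
- The stated 150 lies between the two, within 3% of each.
- Observed at maximum loss: 150 × 0.80 = 120 per group. Lost: 30 per group, 60 of 300.

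No SD or baseline mean is given, so the 122 itself cannot be rebuilt. The standardised difference it implies is (1.645 + 0.842) × √(2/122) = 0.318. At 120 per group, power for that difference is 79.4%. The allowance for loss therefore broadly protects power, but it does nothing about bias.

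Patients without a week-24 value at 5, 10, 15 and 20% loss: 15, 30, 45 and 60 of 300. The sensitivity analysis brings none of them back.

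**3. Illustration of the size**

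Let E be the treatment effect in completers, L the loss (equal in both groups), and f the fraction of E present in lost patients. L is taken from the plan's maximum downwards. f is my assumption, because the document gives nothing on it.

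- All-randomised effect = (1 − L)E + L·f·E = E × (1 − L + L·f)
- Overstatement by completers = 1 / (1 − L + L·f) − 1

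| Loss L | f | All-randomised effect / E | Overstatement |
|---|---|---|---|
| 5% | 0 | 0.95 | about 5% |
| 10% | 0 | 0.90 | about 11% |
| 15% | 0 | 0.85 | about 18% |
| 20% | 0 | 0.80 | 25% |
| 20% | 0.5 | 0.80 + 0.10 = 0.90 | about 11% |
| 20% | 1 | 1.00 | 0 |

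I give ratios because Sample size {14} describes its 20% as a reduction from baseline, so it cannot safely be used as the between-group effect in completers.

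**The case against.** Several stronger readings are tempting, and the text does not support them.

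- **That FAS and PP are the same patients, so the results must agree.** The definitions differ: one depends on four weeks of CBT, the other on the 6-month examinations. PP may include early stoppers whom FAS excludes, and the sets can differ for month 1 and 3 outcomes. What stands is narrower: neither set supplies a week-24 value for a lost patient.
- **That month 1 and 3 values of later dropouts are discarded.** Outcomes are to be compared at those visits too, and an observed-case analysis there would use them. They go unused only in the week-24 comparison.
- **That the effect will be overstated by 25%.** This combines the planned maximum loss with no effect in any lost patient. It is the highest figure in the table and not an estimate.
- **That dropout will differ by arm.** The plan assumes the same maximum in both groups. Assessments continue after treatment stops (section {11b}), and missing data prompt a telephone call (section {18b}). If loss is unrelated to outcome, completers need not overstate anything.
- **That the rules on running PP flatly contradict each other.** The both-sets sentence allows for exceptions, and the 10% trigger can be read as one. What remains is unclear drafting: the document does not say whether the discrepancy is in patient numbers or in results.

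None of this answers the central point. The mitigations may reduce the loss, but no planned analysis would show whether the remaining loss matters.

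**Conclusion.** The point holds for the week-24 primary endpoint. The protocol names a sensitivity analysis to test an assumption about lost patients, and that analysis contains no lost patients. No other planned analysis of this endpoint does either.

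Up to 60 of 300 patients are affected. The possible overstatement runs from zero to 25% over the cases tabulated, depending on actual loss and on the unknown effect in lost patients, with equal loss in both groups assumed. The documents do not show that bias will occur or in what amount. They show that the plan as written could not detect it.

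The conclusion about who is included follows from the definitions alone and needs none of the numerical assumptions. It takes the FAS as meant to include control patients; its wording, which refers only to CBT, is a separate matter.

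**What to change.** 1. **Primary analysis.** Analyse LDL-C change with a repeated-measures model in all randomised patients, using the month 1, 3 and 6 values already scheduled, with the week-24 treatment contrast as the primary comparison. Patients lost after month 1 or 3 then contribute to it. The model is valid under missing at random.
2. **Sensitivity analysis.** Replace the completer analysis in this role with delta-adjusted or reference-based multiple imputation for patients without week-24 data, including those lost before month 1. Set the delta range or the reference rule in advance and report results over the range.
3. **Completer analysis.** Keep it as supportive only, and state that it is always run.
4. **The 10% trigger.** Delete it. It is undefined and sits unclearly beside the rule that analyses are done in both sets.
5. **Section {20b}.** Reword the exclusion of additional analyses so that it does not bar item 2.

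Other repeated-measures or imputation choices would also serve. What matters is that at least one analysis varies the assumption about lost patients.

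Cost: a little more analysis work and a protocol amendment, which section {25} routes through the steering committee and the ethics committee. It should be settled before outcomes are analysed by group. No new data are needed.

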#### Plans to give access to the full protocol, participant level-data, and statistical code {31c}

The results of the clinical trial will be published in the form of articles, but the specific scope and time of publication are yet to be determined. All relevant data and information will be disclosed when the article is published.

### Oversight and monitoring

#### Composition of the coordinating center and trial steering committee {5d}

*Design and conduct of the study*: preparation of protocol and amendments; preparation of IB (investigators brochure) and CRFs (case report forms); reports on studies to be published; composition of TMC’s members.

*SC (steering committee)*: final protocol agreement; patient recruitment and communication with the lead investigator; reviewing the trial’s progress and, if necessary, consenting to adjustments to the protocol and/or investigators brochure to help the study run smoothly. The steering group will include all principal investigators. A regional coordinator will be chosen from among the principal investigators at each site.

*Trial Management Committee (TMC)*: (principal investigator, research physician, administrator): study planning; organization of steering committee meetings; report of adverse events to the Chinese National Adverse Reaction Monitoring Center; responsible for the trial master file; budget management and contractual difficulties with individual centers. randomization; data verification. TMC will examine the 12 monthly feedback forms and schedule site visits; data manager: data entry and maintenance of the trial’s IT system; data verification.

*Lead investigators*: recruitment; data collection; CRF completion, as well as study patient follow-up and adherence to the study protocol and IB. A lead investigator will be assigned to each participating center and will be responsible for patient identification.

#### Composition of the data monitoring committee, its role and reporting structure {21a}

There will be no data monitoring committee as this is considered to be a low-risk intervention.

#### Adverse event reporting and harms {22}

The type and frequencies of any adverse event will be reported to the Chinese National Adverse Reaction Monitoring Center. Any trial deviations and violations will also be sent to the Chinese National Adverse Reaction Monitoring Center.

#### Frequency and plans for auditing trial conduct {23}

Audit procedures will comply with the ICH GCP (Guideline for Good Clinical Practice of the International Conference on Harmonisation) and regulatory requirements.

Project management group meeting will be conducted both weekly and monthly. Weekly meeting will be held every Friday. Monthly meeting will be conducted at the last day of every month. The project management group will audit information on the research. The ethics committee will meet every 6 months.

#### Plans for communicating important protocol amendments to relevant parties (e.g., trial participants, ethical committees) {25}

The steering committee will determine any revisions of the protocol. The amended protocol will also be submitted to the Medical Ethics Committee of the Sir Run Run Shaw Hospital of Zhejiang University and reported to the participants as necessary.

#### Dissemination plans {31a}

The findings of the study will be presented to the public at academic conferences. The steering group will decide on authorship. The order of the authors will be determined by the contributions of each member.

## Discussion

This article presents a detailed description of a multicenter RCT, designed to evaluate the effectiveness of CBT to reduce LDL-C levels in ASCVD patients. The treatment for ASCVD generally involves long-term lifestyle management at home. To accomplish the primary goal of controlling blood lipids, we consider the mobile-based CBT intervention as an available and accessible method to promote healthy habits, and as a result, this will potentially lower LDL-C in ASCVD patients. We believe that mobile-based CBT lifestyle intervention will be potentially effective in lowering LDL-C levels in ASCVD patients.

This study has some critical implications. The novel mobile-based intervention is expected to reduce LDL-C level at a population level due to the high accessibility and availability of technologies. Moreover, this CBT treatment can potentially fill the existing gaps of limited professional lifestyle interventions in ASCVD patients.

There are some limitations of this study. First, it is impossible to blind participants and staff (excluding statistician) in psychotherapy studies due to the nature of the research. As a result, therapy expectancy effects may be a source of bias. Second, mobile-based delivery method may anticipate unexpected challenges including technology issues. We will keep in track any technology difficulties for the participants and any technology issues that happen during the study, to advise mobile-based delivery improvement in the future.

### Trial status

Protocol version: original; version 1.1 20210720

Recruitment start date: August 1, 2021

Anticipated completion of recruitment: December 31, 2021

Actual completion of recruitment: January 2022

## Abbreviations

ACS: Acute coronary syndrome
ASCVD: Atherosclerotic cardiovascular disease
BMI: Body mass index
CBT: Cognitive behavioral therapy
CRC: Clinical research coordinator
CRFs: Case report forms
DM: Data manager
FAS: Full analysis set
GEGS: General Self-Efficacy Scale (GSEs)
HIPAA: Health Insurance Portability and Accountability Act
IB: Investigators brochure
LDL-C: Low-density lipoprotein cholesterol
ICH GCP: Guideline for Good Clinical Practice of the International Conference on Harmonisation
MeSH: Medical subject headings
MI: Myocardial infarction
PP: Per-protocol
QL-index: Quality of life index
SC: Steering committee
SPIRIT: Standard Protocol Items Recommendations for Interventional Trials
TMC: Trial management committee
